### Radiotherapy

3.2

All patients receive a planning computed tomography (CT) scan with a slice thickness of 3 to 5 mm. Afterwards these CT scans are used to outline organs at risk (OARs) and to contour the gross tumor volume (GTV) and clinical target volume (CTV). The GTV was contoured based on the esophageal endoscopy, barium esophagography, and chest CT scans. The clinical target volume (CTV) consisted of the GTV plus a 0.5 to 1 cm circumferential margin, 3 to 4 cm craniocaudal margin and lymph node drainage area. The supraclavicular nodes were included for upper esophageal lesions, and celiac nodes were included for distal esophageal lesions. The planning gross tumor volume (PGTV) consisted of the GTV plus a 0.5 to 1 cm circumferential margin, 3 cm craniocaudal margin. The planning target volume (PTV) consisted of the CTV plus a 0.5 to 1 cm margin for daily set-up error and organ motion. Radiotherapy will be performed as intensity modulated radiotherapy (IMRT), which will be administered beginning on day 1 of chemotherapy using a linear accelerator (energy >6 MV) in 30 to 33 fractions (PTV54–59.4 Gy/30–33 fractions, 1.8 Gy/time dose fractionation; PGTV 60–66 Gy/30–33 fractions, 2 Gy/time dose fractionation, 5 fractions per week [Monday to Friday], one fraction per day).

### Chemotherapy

3.3

The experimental group will receive chemotherapy S-1 70 mg/m^2^ weekly from Monday to Friday until radiotherapy completion, then 2 weeks after completion of radiotherapy, 2 cycles of adjuvant chemotherapy consisting of S-1 70 mg/m^2^ from 1 to 14 days will be administered, each cycle consisting of 21 days. The control group will receive chemotherapy S-1 70 mg/m^2^ for the first 14 and 22 to 35 days, plus cisplatin 25 mg/m^2^ for the first 3 and 22 to 24 days. Two weeks after the end of radiotherapy, 2 cycles of adjuvant chemotherapy consisting of cisplatin 25 mg/m^2^ for the first 3 days and S-1 70 mg/m^2^ from 1 to 14 days will be administered, each cycle consisting of 21 days.

### Data collection and management

3.4

Each case will be completed with a case report. Mianyang Central Hospital is responsible for establishing the database and entering the data, and will use a date acquisition system electronic data management system to manage the data. The main researchers and statistics analyzer will audit the data and lock it. The final version of the statistical plan will be completed and used to analyze the locked data.

*Special data processing*: Principles for evaluation of the effectiveness of the objective. When the month and year are clear, but the day is unknown, the date will be recorded as the fifteenth day of the month. When the year is clear, but the day and month are unknown, the date will be recorded as an intermediate point between the end of the year and the last known date.

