### Assessment of the primary and secondary endpoints

3.5

In this trial, endoscopic complete response (CR) 3 months after completion of treatment will be evaluated as the primary endpoint. Endoscopic CR was defined as the complete disappearance of any tumor ulceration or stenosis with no new lesion (all endoscopic pictures and reports had to be available), observation of the entire esophagus as defined by Tahara et al,^[22]^ but also no CT-scan progression. Biopsies were not mandatory. Tumor responses were assessed during week 15 according to RECIST guidelines.^[23]^ The primary tumor was assessed on CT scan with measure of the vertical length and maximal thickness of the esophageal wall on transverse plane. Secondary endpoints are the toxicity, progression-free survival (PFS), and overall survival (OS). Adverse events will be encoded in accordance with the requirements of Med DRA. Severity of adverse events will be graded according to the NCI-CTC classification criteria. The toxicity of the treatment, including acute and chronic toxicity will continue to be evaluated during treatment and during follow-up (Table 1). Any serious adverse drug reactions will be reported promptly to the hospital ethics committee. An intent-to-treat analysis (on all randomized patients) was planned for all other end points. PFS was defined as the date from randomization to tumor progression or death. OS was measured from date of study entry to date of death.

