**Table 1 T1:**
[figure not shown]
Evaluation of the treatment process.

The following conditions will be recorded at the end of the treatment (every 3 months during year 1–2, every 6 months thereafter):

1.Survival2.Physical condition based on the ECOG performance status score3.A physical examination4.Vital signs5.Electrocardiogram6.A barium meal7.Esophageal endoscopic biopsy (at the first follow-up time, and then at least once a year)8.CT scan for tumor evaluation (at the first follow-up time, and then at least once every 6 months).

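### Minor: the partial-date rules in section 3.4 have no bounds, so a few PFS or OS event dates could contradict what is already known about the patient

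*Protocol article*

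**What the plan says.** Section 3.4 (Data collection and management) has a short paragraph on special data processing, introduced as "Principles for evaluation of the effectiveness of the objective", so the rules concern efficacy dates. It gives two of them:

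- Day missing: "When the month and year are clear, but the day is unknown, the date will be recorded as the fifteenth day of the month".
- Day and month missing: "the date will be recorded as an intermediate point between the end of the year and the last known date".

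The paragraph sets no lower limit for either rule. It does not say what the last known date refers to (last contact, last visit or last tumour assessment), and it does not name the events covered.

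The time-to-event endpoints that depend on such dates are in section 3.5: "PFS was defined as the date from randomization to tumor progression or death", and "OS was measured from date of study entry to date of death". Both are secondary. The primary endpoint is endoscopic complete response 3 months after treatment. Follow-up, listed with Table 1, is "every 3 months during year 1–2, every 6 months thereafter", with "CT scan for tumor evaluation (at the first follow-up time, and then at least once every 6 months").

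**The concern.** An imputed date should be compatible with every fact already recorded for the patient. Because these rules use fixed calendar points without limits, three kinds of incompatible date are possible:

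- a death, or a progression, placed before a contact or assessment that showed it had not yet happened;
- an event placed before randomisation, which gives a negative time that has no meaning in the Kaplan–Meier analysis planned in section 3.6;
- an event placed in a calendar year other than the one on record.

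At stake is the accuracy of individual PFS and OS times, and the avoidance of ad hoc corrections when such records turn up at data cleaning.

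**Working it through.** The plan gives no figure to reproduce here, so the check is calendar arithmetic on the two rules. The inputs are the rules in section 3.4, the endpoint definitions and follow-up intervals in section 3.5, and the October 2016 opening in section 3.8. The patient dates are illustrations.

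**Rule 1, day missing (15th of the known month).** Suppose the patient was last known alive on day *k* of the month of death. The imputed date is early by *k* − 15 days whenever *k* > 15.

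- The largest case with a truly unknown day is *k* = 30 in a 31-day month: death was on the 30th or 31st, and the rule gives the 15th. Error: 30 − 15 = 15 days before last contact.
- *k* = 31 does not count. A patient alive on the 31st who died that month died on the 31st, so the day is known.
- The same arithmetic applies to progression, with *k* the day of the last progression-free assessment.
- Randomised 20 October 2016, event in October 2016, day unknown: time = 15 − 20 = −5 days.

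**Rule 2, only the year *Y* known.** Read as a midpoint, with *L* the last known date:

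imputed date = *L* + (31 December *Y* − *L*) / 2

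- *Can it precede L?* No. The added term is never negative when *L* is on or before 31 December *Y*. Every *L* from 1 October 2016 to 31 December 2019 was tried with *Y* = 2019, with no violations.
- *Can it fall before year Y?* It stays in *Y* only if *L* is at least as far on as 1 January *Y* minus the 364 days from 1 January to 31 December. For *Y* = 2019 that is 2 January 2018: 728 days to 31 December 2019, half is 364, giving 1 January 2019. One day earlier, the interval is 729 days and the midpoint, rounded down, is 31 December 2018.

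| Last known date | Known year | Imputed date | Inside known year? |
|---|---|---|---|
| 1 July 2018 | 2019 | 1 April 2019 | yes |
| 15 January 2018 | 2019 | 7 January 2019 | yes |
| 30 June 2017 | 2019 | 30 September 2018 | no |
| 15 October 2016 | 2018 | 22 November 2017 | no |

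Last row: 15 October 2016 to 31 December 2018 is 730 + 77 = 807 days. Half, rounded down, is 403, which gives 22 November 2017. From there to 1 January 2018 is 40 days, so the imputed death is at least 40 days too early.

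**How the failure relates to follow-up.** With visits every 3 or 6 months, the last contact before year *Y* begins should be no more than about 6 months earlier, and the midpoint then stays inside *Y*. Leaving the year needs about 12 months or more without contact before *Y* starts.

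**The case against.** The case against is substantial.

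- **The analysis plan may supply the bounds.** Section 3.4 announces a final statistical plan, which is not shown, and an article condenses. This would settle the matter if the article were silent. It is not: it states two definite rules, and those rules as written can give impossible dates. A later plan would have to amend them. If it already does, only alignment is needed.
- **The year-only rule does not prescribe an arithmetic mean.** True; a point inside the known year would also satisfy the wording. The midpoint is the natural reading, and a looser one leaves the date unfixed.
- **The failing cases are uncommon.** This stands. The negative time needs an event within days of randomisation whose day is unknown, while the patient is starting daily radiotherapy. The wrong-year case needs a long lapse against the visit schedule; the 15 October 2016 example means no contact since about the time the trial opened. On the other hand, dates known only to the year arise mainly after contact is lost, and the plan expects losses: section 3.1.3 lists withdrawal and poor compliance, and section 3.6 allows 10% dropout.

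A reader might also infer two stronger things that the document does not support. One is that the year-only rule can date a death before the patient was last known alive. It cannot; only the mid-month rule can. The other is that any progression dated before the patient was last known alive is an error. It is not, because patients live on after progression. The relevant limit is the last progression-free assessment.

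**Conclusion.** The gap is real but minor. Under the mid-month rule a death can precede last known alive by up to 15 days, a progression can precede the last progression-free assessment, and an event can precede randomisation. Under the year-only rule, read as a midpoint, an event can fall before the known year if the last known date is before about 2 January of the year preceding it.

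It would be tempting to conclude that the PFS and OS results are unreliable. The document does not support that. The rules are the same in both arms, the mid-month discrepancy is about two weeks at most, the primary endpoint does not use these times, and no effect on an estimate or on the trial's conclusion is shown. The number of partial dates is not given; that few records are affected is a judgement based on the visit schedule. The conclusion also assumes that no unseen analysis plan already bounds the dates.

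**What to change.** Amend section 3.4, or state in the statistical analysis plan that it supersedes that paragraph:

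- **Month and year known:** use the later of the 15th and the last known alive date (for progression, the last progression-free assessment), kept within that month. The floor should be that date itself, not the day after, which can fall in the next month.
- **Year only known:** use the midpoint between (a) the later of 1 January of that year and the last known alive (or progression-free) date and (b) 31 December of that year.
- **Both rules:** never impute before randomisation, and never impute a progression after a known death date.

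With these bounds, the patient last known alive on 30 March who died that month is dated 30 March. The 2018 death with last contact on 15 October 2016 is dated 2 July 2018 (1 January + 364/2 = 182 days). The October 2016 event after randomisation on 20 October gets 0 days instead of −5. Dates that already satisfy the bounds do not change.

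The cost is a few sentences before data lock, with no added data collection and no effect on patients or sample size.

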### Assessment of the primary and secondary endpoints

3.5

In this trial, endoscopic complete response (CR) 3 months after completion of treatment will be evaluated as the primary endpoint. Endoscopic CR was defined as the complete disappearance of any tumor ulceration or stenosis with no new lesion (all endoscopic pictures and reports had to be available), observation of the entire esophagus as defined by Tahara et al,^[22]^ but also no CT-scan progression. Biopsies were not mandatory. Tumor responses were assessed during week 15 according to RECIST guidelines.^[23]^ The primary tumor was assessed on CT scan with measure of the vertical length and maximal thickness of the esophageal wall on transverse plane. Secondary endpoints are the toxicity, progression-free survival (PFS), and overall survival (OS). Adverse events will be encoded in accordance with the requirements of Med DRA. Severity of adverse events will be graded according to the NCI-CTC classification criteria. The toxicity of the treatment, including acute and chronic toxicity will continue to be evaluated during treatment and during follow-up (Table 1). Any serious adverse drug reactions will be reported promptly to the hospital ethics committee. An intent-to-treat analysis (on all randomized patients) was planned for all other end points. PFS was defined as the date from randomization to tumor progression or death. OS was measured from date of study entry to date of death.

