### Statistical analysis and randomization

3.6

At a bilateral test 0.05 significance level and a power of 85%, with a dropout rate for each group of 10%, observe 40% endoscopic CR, and to exclude a lower limit of confidence interval (CI) of 20% CR, the study requires a total of 88 samples. Randomization will be administered centrally by the SPSS. Patients who meet the inclusion criteria will be randomized on a 1:1 basis to one of the 2 groups.

The proportion of patients with a clinical response and their 95% confidence intervals will be calculated and reported. The number and proportion of specific cases will be analyzed. The Chi-square test and Kaplan–Meier method will be used to analyze the rates and severity of disease progression and overall survival rate, respectively, according to NCI-CTCAE (version 4), and a Fisher exact (probability) test will be used to analyze the correlations between clinical outcomes and toxicity.

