## Discussion

4

CRT has been accepted nowadays as the standard nonsurgical treatment for locally advanced EC.^[24]^ For 2 decades, chemotherapy, especially the 2-drug combination of cisplatin plus fluorouracil has been regarded as a standard regimen to treat patients with EC with distant metastases or recurrence.^[25]^ However, some retrospective studies have suggested that for patients with EC receiving radiotherapy combined with 2-drug chemotherapy have the severe toxicity.^[7,13–17]^ Our retrospective analysis of 133 cases of esophageal squamous cell carcinoma with complete statistical data found that for both OS and PFS, there was no significant difference between single and 2-drug chemotherapy combined with synchronous radiotherapy (unpublished). So we design this experiment to compare the complete remission rate of S-1 and S-1 combined with cisplatin in the treatment of esophageal squamous cell carcinoma.

*Expectations*: Compare S-1 plus cisplatin concurrent intensity-modulated radiotherapy for patients with esophageal squamous cell carcinoma, S-1 concurrent intensity-modulated radiotherapy has the same effect and less side effects.

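### Read most naturally, the all-randomized rule in section 3.5 covers toxicity, so any patient who never starts treatment would lower that arm's reported toxicity rate

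*Protocol article*

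**What the plan says.** Section 3.5 of the protocol article opens with a single primary endpoint: "endoscopic complete response (CR) 3 months after completion of treatment will be evaluated as the primary endpoint". After the definition of response come the secondary endpoints, with toxicity first: "Secondary endpoints are the toxicity, progression-free survival (PFS), and overall survival (OS". Several sentences follow on coding, grading and reporting of adverse events, among them: "The toxicity of the treatment, including acute and chronic toxicity will continue to be evaluated during treatment and during follow-up".

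The population rule comes next: "An intent-to-treat analysis (on all randomized patients) was planned for all other end points". The definitions of PFS and OS follow directly.

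The rule names no exception. The article mentions no treated-patients or safety set, and section 3.6 gives no denominator for toxicity. Section 3.4 foresees a final statistical plan, which is not at hand.

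Section 4 states what the trial expects to show: "S-1 concurrent intensity-modulated radiotherapy has the same effect and less side effects".

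**The concern.** Intent-to-treat suits PFS and OS, because every randomized patient can have the event whether treated or not. Toxicity of treatment is different. A patient who withdraws after allocation and before the first dose or fraction cannot have it. Kept in the denominator, that patient counts in effect as free of toxicity, and the arm's rate comes out lower than the rate among those treated.

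Two things are at stake. One is the rate in each arm, which readers will take as the risk of the regimen. The other is the comparison between arms, which carries the safety half of the expected conclusion. The introduction gives the toxicity of two-drug chemoradiotherapy as a reason for the trial, so the denominator should be settled before the data are seen.

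**Working it through.** **1. What the sentence covers.** Two readings are possible.

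- *Other than the primary endpoint.* The section names one primary endpoint and three secondary ones, and the rule is stated for all others without exception. Toxicity is then covered. This is the more natural reading.
- *Other than toxicity.* The rule comes straight after the adverse-event sentences and straight before the PFS and OS definitions. It would then cover the time-to-event endpoints, and toxicity would have no stated population.

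The steps below apply to the first reading.

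**2. Inputs.** The total of 88 and the 1:1 allocation come from section 3.6, so 88 / 2 = 44 per arm. The article gives no toxicity rate and no number of patients expected not to start, so both are assumed and varied. The 10% dropout in section 3.6 is not used as a never-treated rate, because several drop-out criteria in section 3.1.3, such as chemotherapy delay from toxicity, arise after treatment has begun.

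On the 88 itself: an exact single-arm test of 20% against 40%, at one-sided 0.05 and 85% power, needs 40 per arm (13 or more responders; alpha 0.043, power 0.871), and 40 × 1.1 = 44. The stated two-sided level gives 94 to 104 in total, depending on the method. That is a separate matter; this point uses only the 44 per arm.

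**3. Formula.** With *k* non-starters among 44, counted as event-free:

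reported rate = rate among treated × (44 − *k*) / 44

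The relative understatement is *k* / 44.

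| Assumed rate among treated | *k* = 0 | *k* = 1 | *k* = 2 | *k* = 4 |
|---|---|---|---|---|
| 20% | 20.0% | 19.5% | 19.1% | 18.2% |
| 40% | 40.0% | 39.1% | 38.2% | 36.4% |
| 60% | 60.0% | 58.6% | 57.3% | 54.5% |
| Relative understatement | 0 | 2.3% | 4.5% | 9.1% |

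For example, 40% × 40/44 = 36.4%. A treated-patients denominator restores the first column.

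**4. Difference between arms.** Assume 40% with S-1 plus cisplatin and 20% with S-1, a difference of 20 points and a ratio of 0.50.

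| Non-starters (two-drug arm, S-1 arm) | Reported rates | Difference | Ratio |
|---|---|---|---|
| 4, 4 | 36.4%, 18.2% | 18.2 points | 0.50 |
| 4, 0 | 36.4%, 20.0% | 16.4 points | 0.55 |
| 0, 4 | 40.0%, 18.2% | 21.8 points | 0.455 |

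Non-starters can only lower an arm's rate. The difference can shrink or grow, depending on where they fall.

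**The case against.** The strongest objection is that the sentence does not clearly say this. Its place after the adverse-event text allows the reading that toxicity is the endpoint set apart, which is the restriction asked for here. The article also never writes that patients who did not start count as toxicity-free; that follows from the usual meaning of intent-to-treat. A safety set is ordinary content for the unseen statistical plan, and its absence from a condensed article would be no fault.

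Much of this stands. The ambiguity is real, and the counting rule is implied, not written. What does not stand is that nothing is left to correct. The article does more than stay silent: it states a population rule that, on its more natural reading, covers a named endpoint it does not suit. On the other reading the sentence still needs a clause saying what it excludes.

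Three stronger inferences are tempting and are not supported.

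- *That harm will be understated.* This depends on someone not starting. If all 88 start, the rate is unchanged.
- *That the rule must blur the comparison because more patients will refuse in the cisplatin arm.* Section 3.1 says only that both regimens are explained to candidates before treatment. Nothing shows which arm would lose more patients, and the second table shows movement both ways.
- *That the difference could be nearly halved.* Take assumed severe-toxicity rates of 50% and 30%. If 20% of control and 5% of experimental patients do not receive their regimen and are all free of severe toxicity, the rates are 0.80 × 50% = 40% and 0.95 × 30% = 28.5%, a difference of 11.5 points. But control patients who decline cisplatin and take S-1 would still have S-1 toxicity. The control rate is then 0.80 × 50% + 0.20 × 30% = 46%, and the difference is 46 − 28.5 = 17.5 points. The 20% is itself an assumption with no basis in the article.

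**Conclusion.** The point holds in a limited form. On the more natural reading, section 3.5 puts toxicity on an all-randomized denominator, which is the wrong one for a rate of treatment toxicity. The size is conditional: zero if everyone starts, and a relative understatement of about 2% to 9% in an arm with 1 to 4 non-starters of 44. The direction of any effect on the difference between arms cannot be told from the article. These figures assume that non-starters count as event-free and rest on assumed toxicity rates. The statistical plan, which is not shown, may already define a treated set; the published sentence would then need to be brought into line with it. This is a cheap improvement. It gives no reason to doubt the design.

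**What to change.** Reword the rule in section 3.5 so that intent-to-treat on all randomized patients applies to PFS and OS by name. Leave what is planned for response unchanged.

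Add that toxicity is analysed in all patients who received at least one dose of chemotherapy or one fraction of radiotherapy, grouped by the regimen actually started, with all later follow-up counted even if treatment stops early. The same sentence should say how to group a patient who had radiotherapy only, and a control patient who took S-1 but never cisplatin, since section 3.3 gives S-1 on different days in the two arms. Keep an all-randomized toxicity table as a sensitivity analysis, and report the number of non-starters in each arm.

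The cost is a short rewording and one extra table, with no change to sample size, conduct or treatment. The small downside is that the main toxicity comparison is no longer strictly as randomized; the sensitivity table covers that.

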## Introduction

1

Esophageal cancer (EC) is a common malignancy worldwide.^[1]^ Squamous cell carcinoma is the most common histological type of EC worldwide, with a higher incidence in developing nations.^[2]^ In China, in 2015, the total incidence and mortality rates of EC were 477.9 and 375.0 per 100,000 persons, respectively, and over 90% of cases are esophageal squamous cell carcinoma.^[3,4]^ The incidence and mortality of EC ranks third in China. Yanting in Mianyang city is one of the highest risk areas for EC in the world.^[5]^

Surgery, radiation therapy, and chemotherapy are the major treatments for EC. But at initial diagnosis, 40% to 60% of patients are not candidates for surgery.^[6]^ In these patients, definitive chemoradiotherapy (CRT) is the established treatment of choice. Early trials have shown beneficial effects of CRT compared to radiotherapy alone,^[7,8]^ and definite CRT has been shown in smaller studies to be comparable in efficacy to surgery in patients with nonmetastatic disease.^[9,10]^ Concomitant use of chemotherapy and a radiation dose schedule that is more efficient compared to conventional radiotherapy may provide better outcomes in patients with EC.^[11]^ The chemotherapeutic drugs cisplatin and 5-fluorouracil have been most commonly used in studies examining the effects of definitive CRT in EC.^[12]^ However, despite many advances in diagnosis and treatment, the 5-year survival rate for patients diagnosed with EC ranges from 15% to 20%.^[12]^

Chemotherapy regimens are often a 2-drug regimen in concurrent chemotherapy and radiotherapy for EC.^[13]^ However, some retrospective studies have suggested that for patients with EC receiving radiotherapy combined with 5-FU/cisplatin chemotherapy, due to severe toxicity, only 9% to 38.5% of patients completed the planned treatment. In addition, one study showed that patients receiving radiotherapy combined with 5-FU/CDDP chemotherapy experienced a treatment-related mortality as high as 18%.^[7,14–17]^ Therefore, it is necessary to explore the toxicity of the combined program to improve its treatment tolerance and safety.

In recent years, S-1 reflects the good effect, single use or combined with platinum or combined with radiotherapy have achieved good results, especially the S-1 alone with the combination of radiotherapy treatment effect is very good, and achieved good clinical remission rate (CR).^[18–22]^

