#### Drop-out criteria

3.1.3

Criteria that will lead to the drop-out of a patient before completion of this study may be any kind of treatment for medical reasons or impairment that will result in an interruption or early completion of treatment, include:

1.The withdrawal of the informed consent of patients.2.Patient safety events.3.Chemotherapy delays because of toxicity lasting for more than 2 weeks.4.The patient enrolled in another study during the clinical study.5.Patient does not want to continue to participate.6.The compliance of the patient is not sufficient.7.The researchers’ judgment.

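### The intent-to-treat rule is given to the other endpoints, so the primary endpoint, endoscopic complete response, is left outside it or without a clear analysis set

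*Protocol article*

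**What the plan says.** All references are to the protocol article.

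- Section 3.5 sets the primary endpoint: "endoscopic complete response (CR) 3 months after completion of treatment will be evaluated as the primary endpoint". The definition of CR carries a documentation condition: "all endoscopic pictures and reports had to be available". It also requires that CT shows no progression.
- The same section then names toxicity, progression-free survival and overall survival as secondary, describes how adverse events are coded, graded and reported, and adds: "An intent-to-treat analysis (on all randomized patients) was planned for all other end points".
- Section 3.1.3 describes drop-out in general terms as including "impairment that will result in an interruption or early completion of treatment". Its list contains "Chemotherapy delays because of toxicity lasting for more than 2 weeks" and "The compliance of the patient is not sufficient", as well as safety events, the patient's wish and the researchers' judgment.
- Section 3.6 plans 88 patients, randomised 1:1, for an expected CR rate of 40% against a lower limit of 20%, at a two-sided 0.05 level and 85% power, "with a dropout rate for each group of 10" percent.

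Neither section 3.5 nor section 3.6 names the analysis set for CR or says how a missing 3-month endoscopy is counted.

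**The concern.** The intent-to-treat sentence comes in a paragraph that opens with the primary endpoint and then lists the secondary ones. Read in that order, *other* means other than the primary endpoint. The endpoint that decides the trial would then be the one that need not be analysed in all randomised patients.

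This matters because the drop-out triggers arise after randomisation and several are consequences of treatment. The Discussion (section 4) expects fewer side effects with S-1 alone, so the plan itself foresees that toxicity will differ between arms. If patients who stop for toxicity or poor compliance leave the CR denominator, the two sets being compared are no longer the randomised groups. Separately, if drop-outs respond less often than patients who stay, each arm's CR rate is raised against the 20% limit on which the sample size rests, even when both arms lose the same share.

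**Working it through.** **Inputs from the article (section 3.6).** Expected CR 40%, limit to exclude 20%, two-sided 0.05, power 85%, drop-out 10% per group, 88 patients at 1:1, so 44 per arm.

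**Assumptions made here.** Every drop-out is a non-responder, and the unequal drop-out rates below are illustrative. The documents give neither.

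**1. The plan's own figure.** The total of 88 matches a within-arm calculation. For one arm, 20% against 40%, an exact binomial test at one-sided 0.05 reaches 85% power with 40 patients (13 or more CRs: alpha 0.043, power 0.871). Then 40 × 1.1 = 44 per arm and 2 × 44 = 88. At the stated two-sided 0.05, the normal approximation gives 83.7% power with 40 and 86.6% with 44. A two-arm test of 40% against 20% would need 93 per arm. So 88 appears to be built on about 40 evaluable patients per arm, which fits an evaluable-patient reading of the CR analysis.

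**2. Effect on the comparison.** If drop-outs do not respond and are removed, evaluable CR = all-randomised CR / (1 − d), where d is the drop-out rate. With a true all-randomised CR of 40% in both arms:

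| Drop-out, S-1 | Drop-out, S-1 + cisplatin | Evaluable CR, S-1 | Evaluable CR, S-1 + cisplatin | Apparent difference |
|---|---|---|---|---|
| 10% | 10% | 0.40/0.90 = 44.4% | 0.40/0.90 = 44.4% | 0 |
| 5% | 15% | 0.40/0.95 = 42.1% | 0.40/0.85 = 47.1% | −5.0 points |
| 5% | 25% | 0.40/0.95 = 42.1% | 0.40/0.75 = 53.3% | −11.2 points |
| 25% | 5% | 0.40/0.75 = 53.3% | 0.40/0.95 = 42.1% | +11.2 points |

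Direction and size depend on which arm loses more patients. With equal drop-out the difference stays at zero, but both rates are 4.4 points too high.

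**3. Effect within one arm.** Let the true CR rate be 20% among 44 randomised patients, so that X, the number of CRs, is binomial(44, 0.20). For each denominator, take the smallest count whose exact 95% lower limit exceeds 20%, and compute the chance that X reaches it:

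| Denominator | CRs needed | Chance of excluding 20% |
|---|---|---|
| 44 | 15 | 2.0% |
| 40 | 14 | 4.4% |
| 35 | 13 | 8.6% |
| 31 | 12 | 15.4% |

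The planned 10% drop-out (about 40 of 44) roughly doubles the one-sided error.

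**4. Effect of analysing all randomised patients.** If 40% of retained patients respond and 10% drop out and count as non-CR, the CR rate is 0.40 × 0.90 = 36%. With 44 per arm:

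- exact: P(X ≥ 15) with X binomial(44, 0.36) = 65.8%;
- normal approximation: Φ[(0.16 − 1.96 × √(0.16/44)) / √(0.36 × 0.64/44)] = 71.8%.

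Both are below the stated 85%.

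**The case against.** A reader might infer that the plan definitely removes drop-outs from the CR analysis and that the comparison is therefore biased. The documents do not go that far, for four reasons.

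- No section says that drop-outs leave the CR denominator. Section 3.1.3 lists reasons for drop-out and defines no analysis set. This stands: the exclusion is an inference from section 3.5, supported by the 10% allowance.
- The intent-to-treat sentence directly follows the text on toxicity, so *other* could mean other than toxicity, which would put CR under intent-to-treat. This is possible, though less natural, and the sentence would still need rewording.
- The documentation condition sits inside the definition of CR. Read literally, a patient without endoscopy records does not meet CR, which is close to the rule proposed below. But it can equally be read as a condition for being evaluable.
- Bias in the comparison is not certain. The plan assumes 10% drop-out in each group, and equal drop-out with the same response pattern leaves a null difference at zero. If drop-outs would have responded as often as retained patients, the rates would not be inflated either. The Introduction does report that with 5-FU/cisplatin chemoradiotherapy "only 9% to 38.5% of patients completed the planned treatment", but that is a different doublet, and not completing treatment is not the same as lacking a 3-month endoscopy. It is no estimate of drop-out here.

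Two further inferences are also unsupported. One is that intent-to-treat dilutes the toxicity rates: the toxicity population is commonly left to a statistical analysis plan, and under the second reading toxicity is exempt. The other is that survival follow-up ends at drop-out: section 3.1.3 blurs stopping treatment with leaving the study, but does not say so.

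**Conclusion.** The point holds as a defect in what section 3.5 states: the primary endpoint is either excluded from intent-to-treat, which is the natural reading, or has an ambiguous analysis set. If CR is analysed in evaluable patients only, the comparison *can* be biased. The size is about 5 points at an assumed 5% against 15% drop-out and about 11 points at 5% against 25%, in either direction. Within an arm, the chance of wrongly excluding 20% rises from 2.0% to 4.4% at about the planned drop-out and to 15.4% if only 31 of 44 are evaluable. All these figures assume non-responding drop-outs, and the unequal drop-out rates are illustrations rather than forecasts. A separate statistical analysis plan may define the set, but it would have to resolve or override the sentence in section 3.5.

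**What to change.** 1. In section 3.5, state that CR is analysed in all randomised patients as allocated, and that death, progression or no available 3-month endoscopy counts as non-CR.
2. Keep the evaluable-patient analysis as a sensitivity analysis.
3. In section 3.1.3, state that patients who stop treatment without withdrawing consent still have the CR assessment and survival follow-up. This also limits how many patients are counted as non-CR merely for want of an endoscopy.
4. Restate the power in section 3.6 under the new rule.

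Cost: the change is one of wording and adds no patients or procedures to the schedule. The reported CR rate falls, for example to 36% rather than 40% at 10% drop-out, and power with 44 per arm is then about 66% (exact) or 72% (normal approximation) rather than 85%. If 85% had to be kept at a 36% rate, the normal approximation gives (1.96 × √0.16 + 1.036 × √(0.36 × 0.64))² / 0.16² = 64.1, so 65 per arm or 130 in total. Stating the lower power openly is the cheaper course.
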